## Abstract

•Gingivitis is one of the most prevalent diseases that affects 82% of adult population.•This current protocol is effective at reducing the gingival inflammation.•The use of alternate gel application of Chlorhexidine and Metronidazole showed improvement in the treatment of gingivitis.•Need further implementation of the protocol followed by re-assessment.

Gingivitis is one of the most prevalent diseases that affects 82% of adult population.

This current protocol is effective at reducing the gingival inflammation.

The use of alternate gel application of Chlorhexidine and Metronidazole showed improvement in the treatment of gingivitis.

Need further implementation of the protocol followed by re-assessment.

## Introduction

1

Gingivitis is one of the most prevalent diseases that affects 82% of adult population in the United States [1]. Dental plaque has been established as an etiological factor in the development of gingivitis and periodontitis [2]. Plaque is primarily composed of bacteria in a matrix of salivary glycoprotein and extracellular matrix and removal of this bacterial biofilm is the cornerstone in the treatment of gingivitis and periodontitis [3]. Bacterial biofilm is primarily disrupted mechanically by scaling and root planning, however, several studies have shown that mechanical debridement alone sometimes remains insufficient in the removal of flora responsible for the periodontal diseases [4], [5]. Due to this reason chemical plaque removal agents as an adjuvant to mechanical therapy have gained popularity [6], [7], [8].

The ultimate goal is to remove the offending pathogens; therefore, several approaches have been employed to treat gingivitis based on the systemic and topical administration of antimicrobial agents [9], [10]. Since, the prolonged use of systemic antimicrobials can lead to increased antibiotic resistance, nausea and diarrhea; therefore, investigators are now focusing on the development of localized drug delivery systems that can allow maximum concentration on the target site, thus minimizing the potential systemic effects [11], [12].

Several antimicrobials including Chlorhexidine and Metronidazole have been used as an adjuvant to mechanical plaque removal. Chlorhexidine is the gold standard mouthrinse to treat gingivitis. Several studies have proved that adjuvant use of Chlorhexidine does not provide additional benefits on periodontitis. It has s broad antiseptic spectrum and substantivity [13]. It acts by directly altering the integrity of bacterial cell membrane [10], [14], [15]. However, its use is discouraged because of its unpleasant taste and undesirable tooth staining [13].

Metronidazole has been used by several researchers due to its selective antimicrobial activity against the obligate anaerobes. It has been used successfully for the treatment of gingivitis and periodontitis [3]. Meta-analysis has shown the effectiveness of localized use of Metronidazole as an adjunct to scaling and root planning [16]. Miani et al. concluded that the use of Metronidazole gel significantly reduces the total bacterial count in the gingival crevicular fluid [17]. A study conducted by Pradeep et al. [18] showed that both Metronidazole gel and Chlorhexidine gel are effective in the treatment of gingivitis. However, Leiknes et al. indicated that the use of Metronidazole gel does not improve the treatment outcome when used in combination with scaling and root planning [19]. Several chemotherapeutic agents have been compared in the quest for the most effective treatment modality in the cure of various categories of periodontitis. However, there is scarcity of data regarding the effectiveness of Metronidazole and Chlorhexidine gel in the treatment of gingivitis, therefore, it warrants a study.

Since, measurement of the true endpoint of gingivitis and periodontitis is not always possible, therefore, anatomical measurements are considered as the most effective surrogate endpoints for quantifying the periodontal damage [20]. This includes the use of different gingival and periodontal indices to evaluate periodontal diseases [21], [22], [23].

### Null hypothesis

1.1

0.8% Metronidazole gel, 0.2% Chlorhexidine gel and combination of both Metronidazole and Chlorhexidine gels are equally effective in reducing gingival inflammation.

## Methods

2

### Objective

2.1

To compare 0.8% Metronidazole gel, 0.2% Chlorhexidine gel and alternate application of the two gels in reducing gingival inflammation when used for 14 days as an adjuvant with home based oral hygiene instructions.

#### Primary outcome measure

2.1.1

Bleeding index (BOP in percentage) [Two weeks and six weeks]

#### Secondary outcome measures

2.1.2

Oral Hygiene Index [Two weeks and six weeks]Probing depth [Two weeks and six weeks]Gingival Index [Two weeks and six weeks]

### Operational definition

2.2

#### Gingivitis

2.2.1

It is defined as a site‐specific inflammatory condition initiated by dental biofilm accumulation and characterized by gingival redness and edema and the absence of periodontal attachment loss [24].

#### Gingival index (Loe and Silness) [21]

2.2.2

1.No inflammation.2.Mild inflammation, slight change in color, slight edema, no bleeding on probing.3.Moderate inflammation, moderate glazing, redness, bleeding on probing.4.Severe inflammation, marked redness and hypertrophy, ulceration, tendency to spontaneous bleeding.

### Study design

2.3

Triple blind randomized clinical trial.

### Study setting and duration

2.4

Dental clinic, Aga Khan University Hospital, Karachi**.** Six months after approval of synopsis by Ethical research committee of AKUH.

### Sample size

2.5

Sample size is calculated by sample size calculator (sample size determination in health studies, WHO). Pradeep et al. [18] reported that the mean gingival index score at 6 weeks interval in Metronidazole gel group was 1.43 ± 0.27 while the mean gingival index score in Metronidazole and Chlorhexidine combination gel was 1.01 ± 0.38.

Keeping the above difference at the level of significance (α) at 5% and power of study (1-β) at 95%, we need at least 22 observations. We inflated the number to get 30 subjects per group.

Since, we have three experimental groups, so we need a total of 90 subjects.

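### The 95% power in section 2.5 is for a secondary outcome and one of three pairs of arms; no power is stated for the primary outcome, BOP%

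*Protocol article*

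**What the plan says.** All references are to the protocol article.

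- Section 2.1.1 (Primary outcome measure) names one primary outcome: "Bleeding index (BOP in percentage) [Two weeks and six weeks".
- Section 2.1.2 (Secondary outcome measures) lists "Gingival Index [Two weeks and six weeks" among the secondary outcomes.
- Section 2.5 (Sample size) takes its effect from a cited study in which the "mean gingival index score at 6 weeks interval in Metronidazole gel group was 1.43 ± 0.27" and the "mean gingival index score in Metronidazole and Chlorhexidine combination gel was 1.01 ± 0.38". With alpha at 5%, it concludes: "power of study (1-β) at 95%, we need at least 22 observations". Then: "We inflated the number to get 30 subjects per group", which over three groups makes 90.
- Section 1.1 (Null hypothesis) states equal effectiveness of all three treatments, so three pairs of arms are in play.

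The only numerical statement about BOP% is the eligibility threshold of at least 10% in section 2.6.1.

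**The concern.** Section 2.5 presents 95% as the power of the study. The figure belongs to one outcome that the protocol itself ranks as secondary, at one time point, and to one of three pairs. BOP% is a percentage of sites and the gingival index is a four-grade score. A standardised effect on one does not carry over to the other without an argument, and none is given. The two contrasts with chlorhexidine have no planning effect on either outcome.

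This matters because all three arms are active and the null hypothesis is one of equal effectiveness. If BOP% shows no significant difference, the stated 95% could be cited as support for concluding that the gels are equivalent. The calculation gives no basis for that.

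**Working it through.** **Inputs.** From section 2.5: means 1.43 and 1.01, SDs 0.27 and 0.38, alpha 5%, power 95%, 22 observations, 30 per group. Two readings are needed. Alpha is taken as two-sided, because sidedness is not stated. The 22 is taken as per group, because the next sentence raises it to 30 per group.

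**Step 1: reproduce the 22.** Difference = 1.43 − 1.01 = 0.42. For two independent means, normal approximation:

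n per group = 2 (1.96 + 1.645)² × SD² / difference²

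- Larger SD in both arms: 2 × 12.996 × 0.38² / 0.42² = 21.3, so 22. This matches the protocol.
- Both SDs: 12.996 × (0.27² + 0.38²) / 0.42² = 16.01, so 17.

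The 22 is therefore correct and uses the more cautious SD. The standardised effect behind it is 0.42 / 0.38 = 1.11 SD, or 0.42 / 0.330 = 1.27 SD with the root-mean-square SD.

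**Step 2: what the figure covers.**

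| | Sample size calculation | Primary comparison |
|---|---|---|
| Outcome | Gingival index (secondary) | BOP% |
| Time | 6 weeks | 2 and 6 weeks |
| Arms | Metronidazole vs combination | All three |
| Difference and SD given | Yes | No |

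**Step 3: what 30 per arm can detect on BOP%.** With no BOP% difference or SD in the document, only standardised differences can be given. Assumptions: one pairwise comparison, t-test on patient-level means, equal SDs, two-sided. Power is from the noncentral t distribution with 2n − 2 degrees of freedom and noncentrality (difference/SD) × √(n/2), solved for the difference.

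| Per arm | Alpha | 95% power | 80% power |
|---|---|---|---|
| 30 | 0.05 | 0.95 SD | 0.74 SD |
| 30 | 0.05/3 | 1.07 SD | 0.86 SD |
| 22 | 0.05 | 1.11 SD | 0.86 SD (0.8646) |
| 22 | 0.05/3 | 1.26 SD | 1.01 SD |

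The rows at 0.05/3 show a Bonferroni split over three pairs. The protocol states no such adjustment. The rows at 22 show the position if only the uninflated number is evaluable.

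Power at 30 per arm and alpha 0.05, by true difference: 21% at 0.3 SD, 48% at 0.5 SD, 63% at 0.6 SD, 86% at 0.8 SD, 97% at 1.0 SD.

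**Step 4: percentage points.** These follow only from an assumed SD. If the patient-level SD of BOP% were 10 to 20 points (an assumption that nothing in the document anchors), 0.95 SD would be about 9.5 to 19 points.

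**The case against.** The strongest reply is that the gingival index is close to the primary outcome. Sections 1.1 and 2.1 are about gingival inflammation, which the index measures directly. Its grades in section 2.2.2 are partly defined by bleeding on probing, and both measures are scored at six sites per tooth (section 2.9). The planning choices are also cautious for the pair considered: the larger SD was used, and 22 was raised to 30. All of this stands. It makes the mismatch less stark, but a related outcome still does not supply a difference, SD or power for BOP%.

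Three stronger readings are tempting, and the document does not support them.

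- **That the trial is underpowered for BOP%.** If the true BOP% difference is about 1 SD, 30 per arm is ample for one pair at alpha 0.05. Without a BOP% difference and SD, the question cannot be settled either way.
- **That a difference smaller than the planned one would usually be missed.** At alpha 0.05 this holds only below about 0.5 SD. At 0.6 SD and above, detection is more likely than not.
- **That the planning effect comes from a mixed product unlike the alternating regimen of Group C.** Section 1.1 also calls the protocol's own alternating arm a combination, so the word in section 2.5 does not show what the cited study used.

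It is also fair to say that the detectable differences above assume a patient-level t-test, whereas section 3 (Data analysis) names GEE and a Friedman test. They are a guide to scale, not the power of the planned analysis, and the restated text has to say so.

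**Conclusion.** The point holds in a limited form and should be fixed. The 95% in section 2.5 applies to the 6-week gingival index, metronidazole against the combination, with a difference of 0.42, SD 0.38 and 22 per group. It cannot be claimed for BOP% or for either contrast with chlorhexidine, on which the protocol states no power, difference or SD.

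There is no arithmetic error in the 22, and adequacy for BOP% is undetermined, not shown to be lacking. A 95% claim for one BOP% pair would need a difference near 0.95 SD, or 1.07 SD with a three-way split of alpha, under the assumptions in the working. What is at stake is the reading of a non-significant primary result. No estimate, test or allocation changes.

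**What to change.** Keep 90 patients and restate section 2.5, for example:

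> The 95% power refers to the secondary gingival index at 6 weeks, metronidazole vs combination (difference 0.42, SD 0.38, 22 per group). For the primary BOP%, for a single pairwise comparison of patient-level means (t-test, two-sided), 30 per arm gives 95% (80%) power for a difference of 0.95 (0.74) SD at alpha 0.05, or 1.07 (0.86) SD at alpha 0.05/3 for three pairs. With 22 evaluable per arm the differences are 1.11 (0.86) SD at 0.05, or 1.26 (1.01) SD at 0.05/3.

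Add that these figures approximate the planned analysis. If they are converted to percentage points, state the BOP% SD assumed and its source. Add that a non-significant BOP% result will be interpreted through its confidence interval and not as evidence of equal effect.

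The cost is rewording. It can be done although section 4 (Trial status) says recruitment has started, and it needs no extra patients. The downside is a less favourable power statement.

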#### Sampling technique

2.5.1

Convenience sampling.

### Sample selection

2.6

#### Inclusion criteria

2.6.1

•Patients having 20 or more teeth•Systematically healthy patient with no co-morbids•Subjects with clinically confirmed gingivitis (bleeding on probing ≥10%)

#### Exclusion criteria

2.6.2

•Pregnant or lactating females•Subjects with removal or fixed dental prosthesis•History of surgical or nonsurgical periodontal therapy in the last 6 months•Use of antibiotic in the last 30 days•Habit of smoking or use of smokeless tobacco•Allergic to Metronidazole or Chlorhexidine•Presence of any craniofacial syndrome patients•Patients on medications that have effects on gingival conditions such as Nifedipine, Cyclosporine and Phenytoin etc.

### Data collection procedure

2.7

All those patients who fulfilled the inclusion criteria will receive detailed information regarding the study and only those patients will be included who signed an informed consent. The study will be conducted according to the World Medical Association Declaration of Helsinki.

### Training of the examiner

2.8

All participating investigators will be trained on the development of the trial, case selection, measurement techniques, sample collection, data compilation sheets and their precise role in the study. To evaluate the intra-examiner reliability five subjects, not involved in the study will be evaluated twice by each investigator for the measurements at the interval of one week.

### Procedure

2.9

On the first visit after clinical examination, the specially designed baseline study proforma will be filled-in. The bleeding sites, probing depth and the gingival index score will be calculated for all the teeth (six sites per tooth).

Group A subjects will be instructed to apply a standard 0.2 % Chlorhexidine gel (clinica gel) on the marginal gingiva for the next 14 days, twice a day for 3 minutes, after morning and evening tooth brushing.

Group B subjects will be instructed to apply 0.8 % Metronidazole gel (anaerobic gel) twice daily for 2 minutes for two weeks.

Group C subjects will be instructed to apply 0.2% Chlorhexidine gel (clinica gel) on the marginal gingiva after morning tooth brushing and 0.8% Metronidazole gel (anaerobic gel) after evening tooth brushing. Subjects in these groups will receive the detailed and precise instruction and demonstrations on the diurnal alternate application of the two gels.

The application of the topical gels will be halted after 2 weeks and second clinical examination will be carried out for bleeding sites, probing depth and the gingival index score for all the teeth (six sites per tooth). Scaling & polishing of teeth in all three groups and oral hygiene instructions will be reinforced. Subjects will be recalled at 6 weeks for evaluation of gingival and oral hygiene indices. The reading will be recorded in the study proforma.

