## Data analysis

3

Data will be analyzed using SPSS version 20. Descriptive statistics for variables such as age, baseline clinical parameters including probing depth, bleeding sites, gingival index, and oral hygiene index will be computed. An intention to treat analysis approach will be adopted. Generalized estimation equation (GEE) will be run to account for the correlated data (six probing sites per tooth) for the comparison of study arms. Friedman test will be used to assess the bleeding sites among three study groups at the baseline and endpoint. Similarly, gingival index and oral hygiene index in the three groups at baseline, after 2 weeks and 6 weeks will be compared. The level of significance will be kept at 0.05.

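### The Procedure section's visit contents contradict the outcome list and the analysis: BOP and probing depth are not named at 6 weeks, nor OHI at baseline or 2 weeks

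*Protocol article*

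**What the plan says.** **Outcomes (2.1.1 and 2.1.2).** The primary outcome is "Bleeding index (BOP in percentage) [Two weeks and six weeks". The secondary outcomes are "Oral Hygiene Index [Two weeks and six weeks", "Probing depth [Two weeks and six weeks" and "Gingival Index [Two weeks and six weeks". All four measures carry the same two time points.

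**Visit contents (2.9 Procedure).** At the first visit: "The bleeding sites, probing depth and the gingival index score will be calculated for all the teeth (six sites per tooth". At 2 weeks, when gel use stops: "second clinical examination will be carried out for bleeding sites, probing depth and the gingival index score", again at six sites per tooth. For the last visit: "Subjects will be recalled at 6 weeks for evaluation of gingival and oral hygiene indices".

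**Analysis (section 3).** OHI is among the baseline clinical parameters to be summarised. Bleeding sites are to be tested at baseline and at an *endpoint* with no visit attached. In addition, "gingival index and oral hygiene index in the three groups at baseline, after 2 weeks and 6 weeks will be compared".

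**The concern.** The Procedure section itemises what is measured at each of the three visits, and those items do not match what the outcome list and the analysis require. At 6 weeks it names neither bleeding sites nor probing depth. At baseline and 2 weeks it does not name OHI.

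The most important gap is in the primary outcome. Weeks 2 and 6 are not interchangeable: week 2 closes the gel period, scaling and polishing of all three groups is described next, and week 6 therefore reflects a different state. If 6-week bleeding is not charted, the primary outcome shrinks to its 2-week half. Because the endpoint visit is undefined, nothing in the analysis section would show that this had happened, and the choice of visit could be made after the data are seen. Trial status says that recruitment has started, and an item not charted at a visit cannot be recovered later.

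**Working it through.** No computed figure is at stake, so the check is a cross-tabulation of measure by visit.

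**Step 1. Outcome list against Procedure.** The outcome list gives 4 measures × 2 time points = 8 cells.

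| Measure | Required by outcome list | Named in 2.9 at baseline | Named in 2.9 at 2 weeks | Named in 2.9 at 6 weeks |
|---|---|---|---|---|
| BOP / bleeding sites (primary) | 2, 6 weeks | yes | yes | **no** |
| Probing depth | 2, 6 weeks | yes | yes | **no** |
| GI | 2, 6 weeks | yes | yes | yes |
| OHI | 2, 6 weeks | no | **no** | yes |

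Cells covered: BOP at 2 weeks, probing depth at 2 weeks, GI at 2 and 6 weeks, OHI at 6 weeks = 5. Cells without a named measurement: 8 − 5 = 3, namely BOP at 6 weeks, probing depth at 6 weeks and OHI at 2 weeks.

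**Step 2. Analysis against Procedure.**

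- GI: required at baseline, 2 and 6 weeks; named at all three.
- OHI: required at baseline (twice over, for the descriptive summary and for the comparison), 2 and 6 weeks; named at 6 weeks only, so 2 of 3 visits are unnamed. Baseline OHI is not an outcome time point in 2.1.2, so that gap conflicts with section 3 and not with the outcome list.
- Bleeding sites: required at baseline and *endpoint*. If endpoint means 2 weeks, 2.9 supplies the data, but this analysis leaves the 6-week half of the primary outcome untested. If it means 6 weeks, 2.9 names no measurement for it. Neither reading fits 2.1.1 and 2.9 together.

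**Step 3. Could 6-week bleeding be obtained another way?** In the GI definition (2.2.2), grade 2 excludes bleeding on probing, grade 3 includes it, and grade 4 involves a tendency to spontaneous bleeding. If GI is scored site by site at 6 weeks, the share of sites graded 3 or 4 would approximate a bleeding percentage. That is an assumption: 2.9 states six sites per tooth for baseline and 2 weeks and does not repeat it for 6 weeks, and the article specifies no such derivation. No similar route yields 6-week probing depth, or OHI at baseline or 2 weeks.

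**The case against.** The strongest reply is that silence in one narrative paragraph is not a decision not to measure. The 6-week sentence does not say that nothing else is recorded. The outcome list fixes all four measures at both visits, and section 3 plainly intends OHI at all three. The article also refers to a study proforma that is not shown, where item-by-visit detail would normally sit. The primary outcome is itself called an index, so the gingival indices evaluated at 6 weeks might be meant to include it, and GI grading requires bleeding to be assessed in any case.

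Much of this stands. A reader might infer that the 6-week primary outcome cannot be computed, or that OHI is never measured before week 6. The document does not support that. It shows that 2.9 disagrees with the other sections, not what is done in the clinic.

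The reply does not remove the contradiction. Section 2.9 is not merely brief: it lists measurements visit by visit, and the lists differ. It names bleeding sites and the GI score as separate items at baseline and at 2 weeks, and 2.1.1 and 2.1.2 list them as separate outcomes, so reading one into the other at 6 weeks alone is strained. Section 3's intention to analyse OHI at three visits is one side of the conflict, not its resolution.

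**Conclusion.** The point holds as an internal contradiction. As scheduled in 2.9, 3 of the 8 pre-specified outcome-by-visit measurements are not named, one of them a primary-outcome time point. The baseline OHI required by section 3 is not named, and the endpoint visit for the bleeding-site analysis is undefined. The other 5 cells are covered, including BOP at 2 weeks and GI at 6 weeks, the measure and time point on which the sample size (2.5) is based.

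The count assumes that 2.9 is followed as written and that its visit lists are complete. On that footing the trial would lose directly charted 6-week BOP; some of it might be approximated from site-level GI grades, but 6-week probing depth could not be. A reader might also conclude that an outcome or visit should be struck from the endpoint list once some patients have missed it. That does not follow: endpoints belong to the trial, and deleting a pre-specified one during recruitment fits poorly with the stated intention-to-treat approach.

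**What to change.** 1. Amend 2.9 and the proforma so that bleeding sites and probing depth (six sites per tooth), GI and OHI are all recorded at baseline, 2 weeks and 6 weeks. If the proforma already captures them, only the text of 2.9 needs correcting.
2. State in section 3 which visit or visits *endpoint* means for BOP, consistent with the 2- and 6-week time points in 2.1.1, and do so before outcome data are examined by group.
3. For patients already past a visit where an item was not taken, keep the endpoint, treat the value as missing, and report how many values are missing by outcome, visit and group.

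The cost is a few extra minutes of charting per patient (a judgement; the article gives no timings), a proforma edit and an amendment. The visits already exist, and under 2.10 the same investigator takes all the measurements, so no new visit or examiner is needed.
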